### Blinding

This study will use a single-blind design in which both the participants and the primary outcome assessors will remain blinded to group assignments. A designated project manager will oversee the generation of the randomization sequence and the allocation of blinding codes. Group assignments will be generated using a computer-based random number table and anonymized as group A or B.

Given the inherently distinguishable nature of acupuncture interventions, blinding of treating physicians is not feasible. However, all treating physicians will undergo standardized training to ensure consistent procedures and neutral communication, thereby minimizing observer bias.

Participants will be randomly assigned to either the acupuncture group or the conventional treatment group. To maintain participant-level blinding, the conventional treatment group will receive sham acupuncture using specially designed nonpenetrating needles applied to nonacupoint locations. The procedures, including manipulation, duration, and frequency, will be identical in both groups to ensure comparable treatment experiences.

Outcome assessors and statistical analysts will be blinded to the actual group identities and will only have access to anonymized labels (A or B). Conversely, treating physicians and project managers will not participate in outcome assessment or data analysis. Similarly, outcome assessors and analysts will not be involved in participant enrollment or allocation.

The blinding code will be securely sealed and will not be disclosed until the completion of all statistical analyses.

To assess the success of blinding, participants will be asked at the end of the treatment period to indicate which group they believe they were assigned to (A, B, or unsure) via a structured questionnaire.

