### Randomization and Allocation Concealment

An impartial statistician will generate a concealed random allocation sequence using the PLAN procedure in the SAS statistical software (version 9.1; SAS Institute). Eligible participants will be randomly assigned in a 1:1 ratio to either the acupuncture treatment group or the conventional treatment control group. The random sequence will be securely stored and managed by a project manager who is not involved in participant recruitment, screening, or outcome assessment. To ensure allocation concealment, the group assignments will not be disclosed to screeners, evaluators, or participants during the enrollment process. Once a participant is deemed eligible and enrolled, the project manager will inform them of their group assignment via telephone, thus maintaining strict separation between the randomization process and other trial operations.

Given the nature of acupuncture, it is not feasible to blind the practitioners delivering the intervention. We acknowledge that the lack of practitioner blinding could introduce performance bias and influence internal validity through potential nonspecific or placebo effects. To minimize these risks, we will (1) blind participants to the specific study hypotheses and expected effects of each intervention, (2) ensure that outcome assessors and statisticians remain blinded throughout the trial, (3) standardize the practitioner-patient interaction by using scripted instructions and limiting nonprotocol communication, and (4) provide the control group with conventional treatment to control for attention and treatment expectancy effects. These measures aim to reduce expectancy bias and placebo responses, thereby strengthening the internal validity of the trial despite the inherent limitations of acupuncture blinding.

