### Primary Outcomes

All practitioners involved in the study are experienced and professionally trained rehabilitation physicians or therapists. The MoCA will serve as the primary outcome measure for statistical inference as it is more sensitive to detecting MCI and changes in executive and visuospatial domains commonly observed after stroke. The MMSE will be analyzed as a key secondary outcome to provide complementary information and enable comparison with previous literature where the MMSE was the predominant tool.

Both assessments will be administered by the same trained therapist before and after the intervention to ensure consistency and minimize interrater variability. The MoCA evaluates a broad range of cognitive domains, including visuospatial and executive abilities, naming, memory, attention, language, abstraction, delayed recall, and orientation. It consists of 12 subitems, with a total score of 30 points; a score of >26 is generally considered healthy. For participants with <12 years of education, 1 point will be added to the total score to adjust for education bias.

The MMSE also provides a total score of 30 points and assesses domains such as orientation, registration, attention and calculation, recall, language, and praxis. While the MMSE is widely used in clinical settings for its brevity and utility in detecting moderate to severe cognitive impairment, the MoCA is more sensitive to subtle cognitive changes, making it more suitable as the primary statistical end point in this trial.

Multiple comparisons will be addressed by applying Bonferroni or other appropriate correction methods for secondary outcomes, ensuring statistical rigor while capturing a comprehensive and nuanced picture of cognitive changes following acupuncture intervention. The timing of treatment assessments and data collection are shown in Table 1.

**Table 1 table1:** Timing of treatment assessments and data collection.

Item			Study period				
			Before enrollment (−1 wk)	Baseline (0 wk)	Intervention period		
					4 wk		8 wk
Inclusion criteria			✓				
Exclusion criteria			✓				
Informed consent			✓				
Randomization				✓			
Allocation				✓			

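### Outcome assessors are allowed access to the fixed A/B arm label, so one revealed treatment could let a rater infer the arms of other participants rated afterwards

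*Protocol article*

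**What the plan says.** The Blinding section sets up one code for the two arms: "Group assignments will be generated using a computer-based random number table and anonymized as group A or B". It then states who may see it: "Outcome assessors and statistical analysts will be blinded to the actual group identities and will only have access to anonymized labels (A or B". The key linking A and B to the treatments is protected separately: "The blinding code will be securely sealed and will not be disclosed until the completion of all statistical analyses".

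The aim is clear. The same section says that "both the participants and the primary outcome assessors will remain blinded to group assignments", and Randomization and Allocation Concealment lists, among the measures against bias from unblinded practitioners, to "ensure that outcome assessors and statisticians remain blinded throughout the trial". Assessor blinding carries weight here because "blinding of treating physicians is not feasible".

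On the endpoint, Primary Outcomes says: "The MoCA will serve as the primary outcome measure for statistical inference". On who rates, it says: "Both assessments will be administered by the same trained therapist before and after the intervention to ensure consistency and minimize interrater variability". Table 1 schedules the MoCA at baseline, week 4 and week 8. The Discussion (Therapeutic Approaches) concedes that cognitive scales are typically subjective, offers evaluator training as the remedy, and speaks of evaluators in the plural, with one evaluator per patient.

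**The concern.** Masked arm labels are normal for analysts, who cannot compare groups without them. A rater has no such need. A label shared by everyone in an arm tells the rater which participants belong together, so only one further fact, the treatment of any one of them, is missing. Sealing the key does not protect against this, because the key can be worked out from a single known case.

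The arms can be told apart physically in at least one way. The Intervention section has real needles inserted 10 to 15 mm and sham needles that do not penetrate the skin, both five days a week for 8 weeks. The week 4 rating falls during treatment. Because each participant keeps the same rater, what is learned at week 4 is still known at week 8. At stake is the masking of the primary endpoint's ratings, which is one of the plan's main protections against bias.

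**Working it through.** The plan gives no figure to reproduce, so the check is one of reasoning, followed by an illustration on stated assumptions.

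**Who sees what**

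- Blinding: assessors may have access to the A/B label, and the label is the arm under another name.
- Blinding: the sealed item is the A/B key, not the labels.
- Randomization and Allocation Concealment: assignments are withheld from evaluators during enrollment. Beyond that, the section states the aim of continued blinding but no means that would withhold the label.
- Ethical Considerations: coded IDs are mentioned, but for confidentiality. Nothing limits assessors to them.

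So the label is available to raters by an affirmative statement, and nothing elsewhere in the article withdraws it.

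**Reach of one leak**

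- Shared A/B label: every labelled participant that rater sees, up to 54 (27 + 27) with one rater.
- Participant ID only: 1.
- In both cases, only ratings made after the leak can be affected.

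**Illustration**

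Inputs: 54 participants (Sample Size). Assumptions, not in the documents: each participant independently reveals the arm to the rater with probability p, from 1% to 10%; there is either one rater for all 54 or three raters with 18 each.

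- One rater, chance the key is learned: 1 − (1 − p)^54. At p = 1%, 1 − 0.99^54 = 0.419.
- Three raters, chance for a given rater: 1 − (1 − p)^18. At p = 1%, 1 − 0.99^18 = 0.165.
- One rater, participants rated one after another, expected number rated with the key known (counting the one who leaks): the sum over k = 1 to 54 of 1 − (1 − p)^k.
- ID only, expected number revealed: 54p.

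| p | One rater: key learned | Three raters: key learned, per rater | One rater: expected number rated with key known | ID only: expected number revealed |
|---|---|---|---|---|
| 1% | 42% | 17% | 13 | 0.5 |
| 2% | 66% | 30% | 21 | 1.1 |
| 5% | 94% | 60% | 36 | 2.7 |
| 10% | 99.7% | 85% | 45 | 5.4 |

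The fourth column is the fairer comparison with the fifth, since it leaves out participants rated before the leak. It is still a simplification: it treats each participant as rated once, whereas the plan has three visits.

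**The case against.** The strongest reply is that the sentence limits access rather than granting it. It says assessors see no more than anonymized labels, and it may be two roles compressed into one line of a journal article. Nothing says that the code is printed on rating forms or how it reaches the rater, and the trial does use coded IDs. This stands as a limit on certainty: the plain reading is that assessors may see the label, not that they are shown to be handed it for each participant. It does not remove the point, because if IDs only were intended, the sentence is wrong as written.

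Second, the leak routes are narrower than they may seem. Both arms receive needling with the same handling, duration and frequency; the sham is meant to imitate the sensation; and participants are meant to be blinded. A reader might infer that any remark about needling or sensation breaks the code. The documents do not support that, since such a remark fits either arm. A visible puncture mark or bruise is the more telling cue. The upper end of the assumed range for p therefore has no support in the documents, and neither does the lower end.

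Third, the number of raters is not fixed. The requirement for the same therapist before and after treatment describes consistency within a participant. The Discussion's plural allows several raters, while Data Management speaks of a single final assessor. With several raters, a leak stays with one of them unless it is shared.

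Finally, the label discloses no treatment by itself; it only multiplies the effect of a separate unblinding event. That is correct, and it is why this is a recommended correction rather than a fatal flaw.

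**Conclusion.** The point holds in this form: the Blinding section permits raters to see a fixed two-level arm label they do not need, and this turns a leak about one participant into possible knowledge about others rated later by the same person. The reach is up to 54 participants with one rater and fewer with several.

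A reader might go further and conclude that one leak unblinds the whole trial. The documents do not support that: ratings completed before the leak are untouched, and more than one evaluator is possible.

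The probabilities (42% to 99.7% with one rater, about 17% to 85% per rater with three) rest entirely on the assumed p, on independence between participants and on the assumed rater split. They show how the label multiplies a leak, not how likely a leak is.

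Nor do the documents say how far a rater who knew the arm would shift a score. For scale only, the Sample Size section's d = 0.40 with SD 7.5 implies 0.40 × 7.5 = 3.0 MoCA points. An assumed tilt of 0.5 to 1 point would be 0.5/3.0 = 17% to 1/3.0 = 33% of that, and it would apply only to ratings made after a leak. This is not an estimate of bias in this trial.

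**What to change.** Amend the Blinding section to separate the two roles. Outcome assessors see only a participant ID, with no group code on any form, schedule or database view they use. The A/B label is attached to the cleaned, locked dataset and released only to the statistical analysts. The sealed key stays as planned.

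The cost is a sentence or two in the protocol and, if a group field exists in anything assessors use, its removal. No extra patients, visits or staff are needed. The Results section states that no participants have been enrolled as of August 2025, so the change can be in place before the first rating; knowledge a rater has already gained could not be undone later.

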##### Sham Acupuncture Procedure

Sham acupuncture will be administered at nonacupoint sites approximately 2 cm posterior to Baihui (GV20), 1.5 cm lateral to Shenting (GV24), and 2 cm adjacent to Sishencong (EX-HN1), avoiding recognized meridians [40]. A nonpenetrating placebo needle will provide superficial tactile pressure without skin penetration, mimicking real acupuncture sensation but avoiding physiological effects [41]. Sessions will last 20 minutes once daily, 5 days per week for 8 weeks.

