#### Acupuncture Treatment Group

##### Overview

Participants will receive all the aforementioned conventional therapy components and real acupuncture in place of sham acupuncture. Selected acupoints will include GV20, GV24, and EX-HN1. Disposable sterile filiform needles will be inserted to a depth of 10 to 15 mm and manipulated to elicit *deqi* sensation. Each session will last 20 minutes once daily, 5 days per week for 8 weeks.

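### The participant blinding check offers the masking codes A and B as answers, so as written it cannot show whether participants could tell real from sham needling

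*Protocol article*

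**What the plan says.** All references are to the protocol article.

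- **Blinding**, on the codes: "Group assignments will be generated using a computer-based random number table and anonymized as group A or B". Assessors and analysts see only these letters, and "The blinding code will be securely sealed and will not be disclosed until the completion of all statistical analyses".
- **Blinding**, on who is masked: "both the participants and the primary outcome assessors will remain blinded to group assignments".
- **Blinding**, on the check: at the end of treatment participants are asked "to indicate which group they believe they were assigned to (A, B, or unsure) via a structured questionnaire".
- **Randomization and Allocation Concealment**: once a participant is enrolled, "the project manager will inform them of their group assignment via telephone". By grammar the person informed is the participant. The text does not say whether the call conveys the letter or the treatment.
- **Sham Acupuncture Procedure**: "A nonpenetrating placebo needle will provide superficial tactile pressure without skin penetration". In the acupuncture group (Overview), needles are "inserted to a depth of 10 to 15 mm and manipulated to elicit *deqi* sensation".

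The article names no blinding index and no criterion for successful blinding.

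**The concern.** A blinding check is meant to show whether participants formed a correct belief about the treatment they received. Here the two procedures differ in ways a participant might feel, so the belief to be recorded is real versus sham. The answer options record a code letter instead. By the article's own account the letters exist to carry no treatment meaning until the analyses are finished, which is after the questionnaire is completed.

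This is the only check on participant blinding that the article describes, and it supports a strong inference. Practitioners are not blinded, and the Randomization and Allocation Concealment section accepts that placebo effects could follow. The Discussion nevertheless attributes any group difference solely to the acupuncture points. A reader will look to this questionnaire to judge that attribution, and an uninformative answer could be reported either as reassurance or as failure.

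**Working it through.** There is no stated figure to reproduce. The check is to follow the item through each reading that the text allows.

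**Inputs.** From the article: options A, B or unsure; 27 participants per group (Sample Size). Assumed, because the article gives no values: 0% or 30% answer unsure; among those who answer, the true belief about real versus sham is correct 50%, 80% or 100% of the time.

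**Measure, for illustration only.** Per-arm blinding index = (correct − wrong)/n. If a share u is unsure and a share p of the rest is correct, its expectation is (1 − u)(2p − 1). Unblinding is flagged if, in either arm, index − 1.645 × SE > 0, where SE = √{[pc(1 − pc) + pw(1 − pw) + 2·pc·pw]/n} and pc, pw are the proportions correct and wrong out of n.

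**Reading 1: letters unexplained, own label unknown.** Guesses are unrelated to allocation, so p = 0.5 and the index is (1 − u)(2 × 0.5 − 1) = 0, whatever the true belief. With u = 0 and n = 27, an arm is flagged at 18 or more correct:
- at 18, index = 9/27 = 0.333 and 1.645 × SE = 0.298, so it is flagged;
- at 17, index = 7/27 = 0.259 and 1.645 × SE = 0.306, so it is not.

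The chance of 18 or more out of 27 at p = 0.5 is 0.061. For either arm it is 1 − (1 − 0.061)² = 0.118. That is a false-alarm rate and does not move with what participants perceive.

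**Reading 2: the telephone call gives participants their letter.** Everyone who answers is correct, so p = 1 and the index is 1 − u: 1.0 with none unsure, 0.7 with 30% unsure. This holds even if nobody can tell real from sham.

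**Reading 3: the form explains the letters.** The item then works like one with named options, but the meaning of the code is released before the sealed code is due to be opened.

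**Comparison**, n = 27 per arm, 4,000 simulated trials per setting:

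| Item | True belief correct | Mean index, 0% / 30% unsure | Flagged, 0% / 30% unsure |
|---|---|---|---|
| Reading 1 | 50%, 80% or 100% | 0 / 0 | about 12% / about 11% |
| Reading 2 | 50%, 80% or 100% | 1.0 / 0.7 | 100% / 100% |
| Options name the treatment | 50% | 0.00 / 0.00 | 11.8% / 11.1% |
| Options name the treatment | 80% | 0.60 / 0.42 | 99.9% / 99.1% |
| Options name the treatment | 100% | 1.00 / 0.70 | 100% / 100% |

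With 22 per arm the pattern is the same: reading 1 is flagged in 11% to 13% of trials.

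Only the named options follow the truth. Readings 1 and 2 give the same result down the whole range of true belief.

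Reading 1 also assumes that participants share no preference for a letter and no private theory of what it means. If a share q of those answering picks A, the index is (1 − u)(2q − 1) in arm A and (1 − u)(1 − 2q) in arm B. The two sum to zero, so one arm could be flagged through letter preference alone.

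**The case against.** The strongest reply is that the questionnaire is not shown. The letters may be an article's shorthand for worded options, and the question itself, about the group a participant believes they were in, is a usual one. That stands as a reason for caution about what the form says. It does not rescue the published text, which uses for the answers the same letters that it has just defined as masking codes.

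A second reply is that explaining the options on the form need not unmask anyone. That is fair: it would expose the analysts' code only if the form used the same mapping and reached assessors or analysts, and the article does not say who sees the form. The conflict with the sealing rule under reading 3 is therefore a risk, not a certainty.

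A third is that the item enters no efficacy analysis and no sample-size calculation, and that the Limitations already concede that total blinding is hard to achieve. Both are true. Rewording the item changes no treatment estimate; it changes what can be said about blinding.

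Two stronger readings go too far. A reader might infer that the check would report intact blinding whatever the truth. The text does not support this: it is a tendency under reading 1 only, and under reading 2 the check points to failure. A reader might also infer from the telephone sentence that participants will be unblinded. The article does not say what the call conveys, and elsewhere states that participants stay masked; the two passages conflict and need reconciling, but neither proves unblinding.

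**Conclusion.** The point holds as a defect in the stated item. With the masking codes as answers, the check is uninformative about real-versus-sham perception, and its direction depends on whether participants know their own letter: expected index 0 if they do not, and 1.0 (0.7 with 30% unsure) if they do. If the letters are explained so that the item works, their meaning is disclosed before the code is due to be opened.

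The reasoning from the text needs no numerical assumption beyond taking the letters as the article defines them. The index, the flagging rule, the unsure rates and the belief rates are illustrations and do not come from the article. Confidence is limited only by the unseen form. The item should be corrected before enrolment, because beliefs not recorded at the end of treatment cannot be recovered reliably later.

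**What to change.** 1. Replace the answer options with *real acupuncture*, *sham acupuncture* and *do not know*.
2. Keep the letters A and B out of all participant material.
3. Keep the answers from outcome assessors, and from analysts until the main analysis is complete. If most of one lettered group answered *real acupuncture*, the answers would themselves reveal the code.
4. Report the distribution of answers by arm. A blinding index by arm with a confidence interval, a confidence rating and the reason for the guess are useful but optional.
5. Reconcile the telephone sentence in Randomization and Allocation Concealment with the Blinding section: state who is called and what they are told.

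The cost is one reworded questionnaire item, a clarified sentence and a small descriptive table. The Results section reports that nobody had been enrolled as of August 2025, so on that account no data would be affected.

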### Intervention

All participants will receive conventional therapy standardized according to the Chinese guidelines for the diagnosis and treatment of vascular cognitive impairment (2024 edition) [39], with clearly defined components, treatment frequency, and documentation procedures to ensure reproducibility.

